## Abstract

**Background:**

The high prevalence of low back pain (LBP) in today’s working population and its substantial impact on quality of life call for preventive and sustainable strategies. Physical activity (PA), especially during leisure-time (LTPA), has been proposed as one of the few promising, active preventive measures against the onset of LBP. This is the protocol for the prospective observational study *workHealth* that aims to describe the patterns of PA among workers (including back posture and movement), examine the link between PA, LBP and back health and identify theory-based psychological determinants of LTPA.

**Methods:**

The proposed study is a longitudinal observational study taking place over 2 months with an intensive-longitudinal ecological momentary assessment (EMA) phase. A sample of 252 adults will be recruited from two working populations, sedentary workers, and manually working physiotherapists. At baseline, participants complete a self-report questionnaire and undergo an objective measurement of their back posture and mobility. At 2, 4, and 8 weeks after baseline, participants fill in the follow-up questionnaires. Starting at baseline, participants will also wear an accelerometer and will complete three daily questionnaires for the following 14 days. In addition to the main study, a sub-sample of 8 observational *N*-of-1 studies will have an extended EMA phase of 68 days and a data-driven exit interview. The primary outcome is moderate-to-vigorous LTPA. Data will be analyzed using regression and multi-level models. For the *N*-of-1 studies, a mixed-methods approach will be used including dynamic regressions.

**Discussion:**

Rather than solely examining LBP from a pathological perspective, *workHealth* is one of the first studies to investigate psychological, behavioral and biomechanical risk factors *and* protective resources against LBP. The study will offer insight into theory-based, psychological determinants of LTPA and its relationship to both low back pain and back health. Between-person and within-person level analyses will provide insight on group comparisons of average effects and individual patterns of physical activity in daily life, respectively. Understanding these relationships can inform future behavioral interventions and ultimately contribute to prevention efforts against LBP and the promotion of back health.

**Trial registration:**

German Clinical Trials Register DRKS00025296|| https://drks.de/|| Registration date 28/06/2021

**Supplementary Information:**

The online version contains supplementary material available at 10.1186/s12889-025-21873-7.

## Background

Low back pain (LBP) is a highly prevalent health problem in the adult population and is the leading cause for years lived with disability worldwide [1]. In 2020, LBP affected 619 million people worldwide and is expected to affect 843 million people by 2050 [1]. In Germany, 52.9% of adults experienced LBP over the last year [2]. Overall, 15.5% of German adults experience chronic back pain [2] that lasts three months or longer and occurs almost every day. Despite its high prevalence and cause of work-related disability [3], the aetiology, treatment and prevention of LBP and chronic LBP remain unclear. Recent research suggests that the disease burden of LBP could be reduced by more than one-third if modifiable, behavior-related risk factors, such as elevated body mass index (BMI), and behavioral risk factors, such as smoking, occupational physical activity (e.g., bending, lifting, awkward postures), and sedentary behavior (e.g., prolonged sitting) could be reduced or eliminated [1]. This highlights the importance of targeting specific health behaviors, particularly physical activity (PA) and sedentary behavior, for the prevention of LBP. Therefore, the present study aims to describe the PA patterns and their association with LBP and back health in a sample of healthy office workers and physiotherapists. To develop future behavioral interventions, we also aim to identify modifiable, psychological predictors of PA based on behavior change theory.

### Physical activity and low back pain

PA is a relevant variable for the prevention of LBP and is recommended as one integral prevention strategy by health guidelines in the treatment of non-specific LBP (e.g., National guideline for the treatment of non-specific back pain) [4]. There is, however, inconsistent and insufficient evidence on which type, intensity and dose of PA is most beneficial for preventing LBP across different population groups. For example, the reviews by Oliveira et al. [5] and Sitthipornvorakul et al. [6] did not find support for the link of PA and LBP among adults. These results might be explained by differences in the PA characteristics across included studies (e.g., type, intensity and duration), heterogeneity of PA measurements (objective vs. self-reports), and the inclusion of only a small number of studies of low quality. In terms of domain-specific PA, occupational physical activity has been identified as a risk factor for LBP [1]. However, results from pooled cohort studies have shown that leisure-time physical activity (LTPA) can serve as a protective resource against LBP [7, 8]. Therefore, one goal of this study is to investigate which intensity and type of PA are the most appropriate for the primary prevention of LBP and the promotion of back health in two different groups of workers: sedentary office workers and physiotherapists.

Previous research indicates that inverted pain ratings are not merely comfort ratings suggesting that pain and comfort are two distinct constructs [9–11]. Recognizing that the absence or a low level of low back pain does not necessarily indicate comfort or good health, the workHealth study introduces a measure of subjective health related to the lower back and will investigate its link with PA.

### Understanding physical activity in workers: integrating theory-based concepts from occupational, health, and pain psychology

Understanding the links between different characteristics of PA, back health and LBP helps to identify target behaviors for future interventions. Theories of behavior change and pain development, on the other hand, can help us to better understand and target the psychological predictors that contribute to the prevention of LBP [12, 13] and the engagement in PA. To do so, the present study draws upon theories from pain (fear avoidance model; avoidance-endurance model of pain) [14–16], occupational (physical activity-mediated Demand-Control model, pamDC) [17] and health psychology (Health Action Process Approach, HAPA; Physical Activity Adoption and Maintenance, PAAM) [18, 19] and integrates these in the Back Health Behavior Model (BHBM; Fig. 1). This model allows for a more nuanced understanding of LTPA adoption in the context of low back pain prevention, acknowledging that LTPA (a) can be understood as a proactive way to cope with LBP (i.e., approach behavior/confrontation) which is partially determined by individuals’ beliefs about their back and pain, that LTPA is (b) dependent on other life domains, such as the workplace, affecting individuals’ general self-determination [20] and capacity to pursue their goals, and that LTPA is (c) not solely the result of conscious intention but also shaped by implicit processes, such as affective states and habits [21, 22].

**Fig. 1 Fig1:**
[figure not shown]
Theoretical framework of the workHealth study: Back Health Behavior Model (BHBM)

### Temporal resolution in prevention research

Previous studies assessing psychological predictors of LTPA and LBP have mainly employed prospective designs across several weeks or months, looking at between-group comparisons of average effects, e.g [23]. Psychological factors that frequently correlate with LTPA (e.g., intention, fear of movement) are often unstable and tend to fluctuate within individuals. These factors should be explored, as they change across time in daily life, e.g [24]. Therefore, in the present study, we also adopt a within-person design to examine individual patterns of LTPA in daily life and to identify the strongest predictors of outcomes.

### Aims and research questions

#### Between-person research questions

This observational study aims to (a) describe the health status of the lower back and PA patterns of working people, to (b) examine the relationship between LBP, back health (i.e., behavior-related outcomes) with PA, and to (c) examine theory-based, psychological predictors of workers’ LTPA. At the macro level, we will describe physical activity patterns in workers’ daily lives in terms of intensity, frequency, duration, and type of activity. At the micro level, we will describe posture and movement of the back using self-reported and objective biomechanical measures. We will analyze the back health and physical activity patterns of people in different work contexts. This includes people who work in a sedentary environment (e.g., office work) and people who do manual work as part of their job, such as physiotherapists.

We hypothesize that individuals from different work contexts will differ in their back health and in their levels of LTPA. We also hypothesize that overall higher mean levels of LTPA will be positively associated with workers’ subjective back health, posture and mobility, and negatively associated with pain. Figure 1 shows the set of theory-based, psychological predictors of LTPA intention and LTPA. Based on the Back Health Behavior Model (Fig. 1) we have the following hypotheses. We hypothesize that overall higher mean levels in activity-related cognitions will be positively associated with LTPA intention, with the exception of risk perception and negative outcome expectancies, for which we expect the opposite. We also hypothesize that overall higher mean levels of back-related beliefs, negative affect, and job demands will be negatively associated with LTPA intention. For positive affect, habit, and job resources, we expect positive associations with LTPA intention. We expect a positive association between overall higher mean levels of LTPA motivation and volitional strategies of self-regulation as well as job resources, and the opposite for job demands. Finally, we hypothesize overall higher mean levels of LTPA to be predicted by volitional strategies of self-regulation. We will also explore whether the relationship between back health and job demands and job resources is mediated by LTPA.

#### Within-person research questions

At the within-person level, we hypothesize that higher-than-usual levels of LTPA are positively linked with low back health. We will examine these associations concurrently (same-day, t) and prospectively (from previous-day, t-1 to next day, t). We also expect individuals to engage in more LTPA than usual on days when their positive affect is higher and their negative affect is lower than usual. On days when individuals experience higher levels of job demands and lower levels of job resources than usual, we expect people to engage in lower levels of LTPA than usual. We will examine these associations concurrently (same-day, t) and prospectively (from previous-day, t-1 to next day, t). We will also describe day-to-day fluctuations in activity-related intention, low back pain, social support, planning, self-efficacy, and plan enactment.

In an additional, observational *N*-of-1 time-series approach including data-prompted interviews, we will examine whether these within-person predictors also hold relevance for a single individual. Qualitatively, we aim to understand the related mindsets, and the struggles, and resources involved in carrying out LTPA. This study expands on previous research by examining not only personal predictors but also the impact of social and work environments on low back health. Furthermore, we investigate strategies individuals use to maintain low back health.

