**Affect**				
How do you feel at the moment? nervous (Item 1), alert (Item 2), upset (Item 3), scared (Item 4), inspired (Item 5), enthusiastic (Item 6), afraid (Item 7), determined (Item 8), irritable (Item 9), excited (Item 10), stressed (Item 11), sad (Item 12) *1 (very slightly or not at all) – 2 (a little) – 3 (moderately) – 4 (quite a bit) – 5 (extremely)*		x	x	-

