##### Objective EMA measures

For accelerometry we use the Move4 [67] which is a sensor based on triaxial acceleration, gyroscope, barometric air pressure, and temperature. It measures acceleration with a measurement range of ± 16 g and an output rate of 64 Hz, for further specifications, see [68]. Raw data is downloaded from the accelerometers via the SensorManager (movisens GmbH). The accelerometer determines the non-wear time in 30 s intervals [69]. Self-reported data on leisure-/work time information (Table 2, ambulatory assessment, e.g., 9:30 am- 4:30 pm) is checked for plausibility, corrected, and combined with the accelerometer signal by an Octave (GNU Octave, version 7.1.0) script provided by movisens. This enriched raw data is run through the DataAnalyzer software (movisens GmbH, version 1.16.3) to obtain 60 s outputs. Following proprietary algorithms [70], the DataAnalyzer produces physical activity intensity and energy expenditure results based on activity-related regression models, fed by participant characteristics (gender, age, weight, height). Results contain minute-by-minute METs (1 MET equals the energy expenditure at rest), steps, and energy expenditure in calories. MVPA outside of working hours is based on MET-values > 3 MET. Light physical activity is categorized for > 1.5–3 MET. By combination with self-reported work time, LTPA is available on a minute-by-minute basis and will be the main outcome measure of the EMA study. Daily wear time is calculated by subtracting non-wear time from the daily recording time (e.g., 24 h). Following Troiano, Berrigan [71], days with ≥ 10 h of wear time will be considered valid. Participants with ≥ 3 valid days will be included in the data analysis [72]. We will check and potentially control for the initial elevation bias [73].

Sedentary behavior is operationally defined as any behavior in a sitting, reclining, or lying position with ≤ 1.5 MET, excluding sleep [74, 75]. Minute-by-minute sedentary behavior during leisure-time and at work are used as a secondary outcome. To maximise the amount of data available for PA, participants will be reminded to charge their Move4 device every 5 days. If participants agree, we will also contact them via their study smartphone 1 week into the study to see if there are any technical problems with any of the devices.

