#### Hypothesis tests for intensive-longitudinal phase

For the IL data with measurement days nested in participants, multilevel models with daily LTPA as outcome will be calculated. Hypothesis tests for the fixed effects will inform us on the daily links between LTPA and its within- and between-person predictors. To test mechanisms from the back health behavior model (Fig. 1), we will specify within-person mediation models and test the indirect effects.

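### Same-day models count leisure activity done before the affect rating as part of the outcome, so they cannot separate affect driving activity from activity driving affect

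*Protocol article*

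**What the plan says.** All references are to the protocol article.

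- **Hypothesis** (Within-person research questions): "We also expect individuals to engage in more LTPA than usual on days when their positive affect is higher" and negative affect lower. Higher job demands and lower job resources are expected to go with less LTPA. The analysis is planned in two forms: "We will examine these associations concurrently (same-day, t") and "prospectively (from previous-day, t-1 to next day, t").
- **Model** (Hypothesis tests for intensive-longitudinal phase): "multilevel models with daily LTPA as outcome will be calculated". The ratings are given the role of predictors: "Hypothesis tests for the fixed effects will inform us on the daily links between LTPA and its within- and between-person predictors". The section adds that "we will specify within-person mediation models and test the indirect effects", without giving a lag.
- **Outcome** (Objective EMA measures): LTPA is activity above 3 MET outside self-reported working hours. "LTPA is available on a minute-by-minute basis and will be the main outcome measure of the EMA study".
- **Timing** (Study design and procedures): prompts come at 8 am, 3 pm and 9 pm, each open for 3 h.
- **Ratings** (Table 2): affect is momentary ("How do you feel at the moment") and marked for morning and afternoon. Time pressure and job control are asked in the afternoon only and refer to that day's work. Recovery experience is asked in the evening, about that evening. The section on determinants lists it among the job resources.
- **Inconsistency:** Self-report EMA measures names affect under the morning measures only, which does not match Table 2.

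**The concern.** A predictor should be measured before the outcome it is meant to explain. Here the outcome is a daily total, and the rating is taken part-way through the day. An early run, a lunchtime session, or most of the activity on a day off can come before the rating and still be counted in the outcome. If activity lifts mood, a positive same-day slope appears even when mood has no influence on later activity.

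The study wants to use these links to identify determinants of LTPA and to test mechanisms. Under Strengths, challenges and limitations it also stresses the temporal order of its theory. A same-day slope read as prediction, or carried into an indirect effect, would support a statement that the data ordering does not allow. The mismatch over when affect is asked adds to this, because more of the day's activity precedes the afternoon score than the morning one.

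**Working it through.** The documents give no figure for this point, so there is none to reproduce. The check has two parts.

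**1. Time order, by predictor.** The latest possible answer is the prompt time plus 3 h.

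| Rating | Prompt | Latest answer | Activity that can precede it |
|---|---|---|---|
| Affect, morning | 8 am | 11 am | Early exercise; little on most workdays, more on days off |
| Affect, afternoon | 3 pm | 6 pm | Early, lunchtime and post-work activity; much of a day off |
| Time pressure, job control | 3 pm | 6 pm | As above, but the items recall work, so leisure activity is less likely to change the answer |
| Recovery experience | 9 pm | midnight | Nearly all of the day's leisure activity |

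In the previous-day model the rating on day t-1 comes before all activity on day t, so there is no overlap.

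**2. Size of the spurious link.** Suppose the rating has no effect on later activity. Within person, scale daily LTPA to variance 1 and split it as total = pre + post, with Var(pre) = s. Let the rating have correlation r with pre and none with post, and let pre and post be independent. Then

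Corr(rating, total) = Cov(rating, pre) = r·√s.

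The documents give neither s nor r, so both are assumed.

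| s | r | r·√s |
|---|---|---|
| 0.05 | 0.1 | 0.1 × 0.224 = 0.022 |
| 0.20 | 0.1 | 0.1 × 0.447 = 0.045 |
| 0.20 | 0.2 | 0.2 × 0.447 = 0.089 |
| 0.50 | 0.3 | 0.3 × 0.707 = 0.212 |

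**Chance of a significant result.** Take 210 people over 14 days, both figures from the Power analysis section. After person-mean centring, df = 210 × 13 − 1 = 2729. The expected test statistic is ρ·√(df/(1 − ρ²)), with √2729 = 52.2.

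- ρ = 0.022: 1.17, so a two-sided 5% test rejects about 21% of the time (19% in 200 simulated studies).
- ρ = 0.045: 2.34, about 65% (69% simulated).
- ρ = 0.089: 4.69, over 99% (98% simulated).

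With fewer usable days the rates fall. At an assumed 202 people and 11 days, s = 0.20 and r = 0.1 give df = 202 × 10 − 1 = 2019, a statistic of 2.01 and about 52% rejection.

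**After the change.** In the same simulations, counting only post-rating activity gave mean correlations between −0.002 and 0.002. The previous-day model gave −0.001 to −0.015, a small negative bias from centring over 14 days.

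The simulations treat pre- and post-rating activity as independent. If they are correlated within a day, the post-rating outcome alone is not clean, which is why the fix also adjusts for earlier activity.

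**The case against.** The best defence is that the plan is less directional than it can be made to look. It calls the same-day analysis concurrent and sets it against a prospective one in the same sentence. The hypothesis is about what happens on days with better mood, and the analysis section speaks of daily links. A daily total answers that question. The article also gives no aggregation rule for daily LTPA, and a condensed article may leave that rule to an analysis plan. Minute-level data leave a post-rating window open.

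Much of this stands. A reader might infer that all within-person results would show reverse effects as prediction. The documents do not support that, because the previous-day models are free of the overlap. A reader might also infer that the mediation models are same-day. The article does not give their lag, so the criticism reaches only mediation that is run same-day. Nor are all ratings equally exposed: time pressure and job control are afternoon recall of work, for which a reverse effect is less plausible. The size rests wholly on assumed inputs.

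What remains is that the article names a daily outcome, fixes the prompt times, gives the ratings the role of predictors and tests indirect effects. The concurrent label does not undo that role. The previous-day model, although sound, does not ask whether mood today precedes activity today.

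A fair warning also applies to the remedy. Answers can be delayed by up to 3 h, and the delay may depend on whether the person was exercising. A window that starts at the answer could therefore be cut short in a way related to activity.

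**Conclusion.** The point holds in a limited form. As described, the same-day models with affect as predictor place pre-rating leisure activity in the outcome, so reverse effects cannot be separated in those estimates or in any mediation run on same-day data. The exposure is greatest for afternoon affect and for days off, and strong for recovery experience. It is smaller for 8 am ratings on workdays and less plausible for time pressure and job control. The previous-day models are not affected.

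The bias may be slight (correlation about 0.02 at s = 5%, r = 0.1) or enough to produce a significant result almost every time (about 0.09 at s = 20%, r = 0.2). The documents give no basis for choosing within that range. A whole-day same-day slope is acceptable as an association and should not be read as prediction.

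**What to change.** 1. Keep the whole-day same-day model and describe it as a concurrent association only.
2. For affect, add a same-day model whose outcome is leisure MVPA minutes after the rating, adjusted for leisure MVPA earlier that day and for leisure wear time after the rating.
3. As a sensitivity check, start the outcome at a fixed clock time, the end of the response window (11 am for morning affect, 6 pm for afternoon affect). The window then no longer depends on response delay.
4. Base directional and mediation statements on time-ordered models, either post-rating or previous-day to next-day, and state the lag used in each mediation model.
5. Do not treat evening-rated recovery experience as a predictor of LTPA on the same day.
6. Reconcile Self-report EMA measures with Table 2 on when affect is asked, and state which affect score enters each model.

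No new data collection is planned for this. The sensor output is per minute, so the work is analysis code. Item 2 needs stored completion times, which the article does not mention; item 3 does not. The cost is fewer outcome minutes per day, above all with the 6 pm cut, and one additional analysis to report.
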